## 1. INTRODUCTION AND RATIONALE

The annual rate for first ever stroke in the Netherlands is estimated about 41.000 persons, with a prevalence of about 216.500. The costs incurred by the care of stroke patients are extremely high and are estimated to exceed one billion Euros in the Netherlands. A recent analysis of initial and secondary care costs of Stroke in the United Kingdom showed that inpatient rehabilitation accounted for about 44% of all costs. In addition, a recent meta-analysis involving 14 trials (1957 patients) has shown that early supported discharge (ESD) with additional services in the community is beneficial in optimizing the transition from the rehabilitation setting to independent living and cost-effective by reducing the length of stay (LOS) of inpatient services and long term dependency of stroke patients. Several RCT's and longitudinal studies have shown that ESD is enabled as soon as patients are independent in their transfers and gait, suggesting that ESD is heavily dependent on balance and motor control of the lower limb. Exercise therapy typically focuses on restoring and/or improving motor function and performance of activities of daily living with the aim to enhance independence. Several systematic reviews have indicated that additional exercise therapy and repetitive task training have a significant effect on functional outcome after stroke, concluding that that more exercise therapy is better.

Guidelines in the Netherlands conclude therefore that patients who are in a rehabilitation setting should have the opportunity to receive a minimal dose of 40 to 60 minutes exercise therapy. In the same vein, the UK guidelines in the United Kingdom recommends a daily dose of 45 minutes of exercise therapy in the early stages after stroke.

At this moment, most patients admitted to hospital stroke units (HSU), rehabilitations Centres (RC) and nursing homes (NH) spend most of their waking time during workdays and weekends being physically inactive or involved in activities that contribute little to their recovery. A recent survey in the Netherlands of 91 hospital Stroke Units showed that patients receive about 24 minutes of exercise therapy each working day, whereas a policy for rehabilitation in the weekends is lacking. Acknowledging that the resources (mostly staff) in the HSUs, RCs and NH's are not sufficient to meet the minimal dose of exercise therapy "novel" methods to increase the duration and intensity of exercise therapy with minimal use of resources are needed. For example, we recently showed that task-oriented group training sessions of 6 to 8 stroke patients simultaneously (ie, circuit class training; CCT) given by a physiotherapist and a sport instructor is an equally effective strategy as an individual face-to-face approach for patients suffering from a stroke.

An alternative method could be to involve caregivers in exercise training. The concept of caregiver mediated exercise (CME) has been tested in a pilotstudy in Reade. Given the experience gained in this pilot study, CME can be considered feasible and safe for both patients en caregivers. To date, a limited number of studies about CME in patients with

stroke has been published. Three of these are randomized controlled trials. Galvin et al studied the added value of a 'family mediated exercise intervention' (FAME) in a HSU. They found that a program of additional daily exercises with a partner aimed at the lower extremity significantly improved the functional outcome of the lower extremity, balance, walking ability and activities of daily living, compared to usual care in a hospital stroke unit. Markedly, the experienced strain of the caregiver measured on the caregiver strain index significantly decreased. One other relevant economic study by Patel et al found that training of the caregiver in the techniques of nursing and facilitation of personal care significantly reduces total health and social care costs for stroke patients over one year, mainly due to reductions in length of hospital stay.

Recently, Gregory et al. recommended a crucial role of e-Health and ICT support for the coordination of caregiver-mediated interventions. However, none of the existing studies however have combined e-Health services with Caregiver Mediated Exercise to enhance Early Supported Discharge. .

The present type I cost-effectiveness study will serve as basis for a future cluster stepped-wedge randomized phase III clinical trial to investigate the cost-effectiveness of the CARE4STROKE program, in which Caregiver Mediated Exercise is combined with e-Health services aimed at Early Supported Discharge

We hypothesize that the CARE4STROKE program will:

- 1) be feasible and safe to execute;
- 2) allows ESD of patient to their own home setting with a significant reduced inpatient stay of 1 day for HSU and 7 days for RC/NH.
- 3) increase patients self-reported health status with concomitant reduced levels of caregiver burden and
- 4) enhance feelings of empowerment as perceived by patient and partner when compared to usual care..

## 2. OBJECTIVES

The CARE4STROKE program is directed at improving self-reported health status and reduce LOS and costs by allowing ESD of stroke patients to their own home setting. ESD from setting of admission will be enhanced by: 1) starting CME applied by a PT focused on gait and gait-related activities immediately after admission in a HSU, RC NH and 2) continuous weekly support by a PT in patients own home setting after discharge with support of e-Health services. The e-Health services will contain the following package: 1) an app with CME for 8 weeks, starting immediately after admission; 2) telerehabilitation services allowing instructions of the PT including monitoring progress of patients and adherence of caregiver and 3) telephone and video conferencing based counseling and weekly visits by a coordinating PT from the setting of discharge focused on increasing feelings of empowerment and self-management of the caregiver.

The main aim of the present pilot study is to investigate feasibility, clinical effectiveness and cost-effectiveness of a caregiver-mediated exercise program (CARE4STROKE) combined with e-Health services, to be evaluated in terms of self-reported health status and mean LOS in stroke patients who are admitted at a HSU, RC or NH and discharged to their own home setting, as compared to usual care.

### 3. STUDY DESIGN

This pilot study has a randomized controlled trial design in a HSU, RC and NH. Within each center 22 patients will be randomly allocated to either usual care + CARE4STROKE program or usual care. Patients will start immediately after admission, continue for 8 weeks irrespective of time of discharge and will be followed-up for 12 weeks.

[figure not shown]

## 4. STUDY POPULATION

### 4.1 Population (base)

Sixty-six patients with stroke and their caregiver will be recruited for this study. Patients with stroke, who are admitted to a participating HSU, RC or NH, and their caregivers will be asked to participate in this study at the moment of admission. There will be no restrictions in relation between patient and caregiver, i.e. the caregiver can be a partner, family member, neighbour or other person close to the patient. The patient has to grant explicit permission as to the choice of the caregiver. There will be a maximum of two caregivers per patient.

Inclusion criteria for the patient:

- 1) 18 years or older
- 2) written informed consent
- 3) able to understand the Dutch language (on sufficient level to understand instructions and complete the questionnaires)
- 4) knowing and able to appoint a caregiver who he/she wants to participate in the programme (with a maximum of two caregivers)
- 5) living independently before the stroke
- 6) planned to be discharged home
- 7) being able to follow instructions (a MMSE score > 18 points)
- 8) Functional Ambulation Score (FAC) < 5
- 9) a score of <11 on the domain "depression" of the Hospital Anxiety and Depression Scale (HADS)
- 10) Motivated for CME

Inclusion criteria for the caregiver:

- 1) 18 years or older
- 2) written informed consent
- 3) able to understand the Dutch language (on sufficient level to understand instructions and complete the questionnaires)
- 4) sufficiently motivated for CME
- 5) a score of <11 on the domain "depression" of the Hospital Anxiety and Depression Scale (HADS)
- 6) medically stable and physically able to perform the exercises together with the patient.
- 7) No significant Caregiver Strain (<4 SCI)

#### **4.2 Exclusion criteria**

Exclusion criteria for both patient and caregiver will be serious comorbidity which interferes with participation.

To determine suitability of both patient and partner, an intake exercise session together with a trained therapist will be scheduled prior to inclusion. The therapist will check the inclusion/exclusion criteria and judge if the exercises can be done adequately and safely.

#### **4.3 Sample size calculation**

We expect a significant reduction of 5 points (11%) on the SIS mobility domain  [ mean 79,4, sd 14] in favor of the experimental training group. We expect that minimally 30 patients are required per arm of the trial. Including 10% dropouts, we suppose that a minimum of 66 stroke patients, (i.e. 22 per centre), are needed to achieve a sufficient statistical power of 80% using a significance level alpha of  $p < 0.05$ .

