## 8. STATISTICAL ANALYSIS

### 8.1 Univariate analysis

Baseline characteristics as described in par 6.1.2 will be presented and between group differences will be studied to determine whether groups are comparable at baseline.

When these data are not normally distributed, non parametric wilcoxon signed rank sum test will be used. When the data are normally distributed student t-test will be used. The  $\alpha$  will be set at 0,05.

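### Section 4.3 claims 80% power for a 5-point SIS-mobility difference, but its own inputs give about 27% in a two-sided, unadjusted comparison, and the 5 points do not match the 11% beside them

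*Protocol*

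**What the plan says.** Protocol section 4.3 rests the sample size on one quantity: "We expect a significant reduction of 5 points (11%) on the SIS mobility domain", in favour of the experimental group, with a mean of 79.4 and an SD of 14 taken from a cited trial. It continues: "We expect that minimally 30 patients are required per arm of the trial". "Including 10% dropouts", this becomes "a minimum of 66 stroke patients, (i.e. 22 per centre), are needed to achieve a sufficient statistical power of 80" per cent. The alpha is 0.05 in section 4.3, and section 8.1 gives the same value. Neither section says whether the test is one-sided or two-sided.

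The Summary lists the SIS as one of two primary measurements, beside length of stay. The third hypothesis in section 1 is that the programme will "increase patients self-reported health status". Section 8.2 plans a multilevel regression with time, group and location, and with baseline values where these are significant. Outcomes are measured at baseline, at 8 weeks and at 12 weeks (sections 6.1.1 and 6.3). No correlation between visits is given anywhere.

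**The concern.** A 5-point difference with an SD of 14 is a standardised effect of 0.36. Thirty patients per arm is far too few to detect an effect of that size with 80% power in an ordinary two-group comparison. The sentence that states the effect has two further problems. Five points is not 11% of the only mean printed, and a reduction is described as favouring the experimental group although the hypothesis is an increase.

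What is at stake is how the result will be read. With 80% power on record, a non-significant SIS result would pass as evidence from an adequately powered trial. If the true benefit were 5 points, the unadjusted comparison would miss it almost three times in four.

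**Working it through.** **Inputs from section 4.3:** difference 5 points (also labelled 11%), mean 79.4, SD 14, 30 evaluable per arm, 10% dropout, alpha 0.05, claimed power 80%. **Assumed, because not stated:** a two-sided, unadjusted two-sample t-test at one time point.

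**1. The plan's own figures.** The headcount reproduces: 2 × 30 × 1.1 = 66 = 3 × 22. (Dividing by 0.9 gives 67, a trivial difference.) The 30 per arm does not reproduce. The required number per arm is n = 2 × SD² × (1.96 + 0.84)² / difference² = 2 × 196 × 7.85 / 25 ≈ 123.1, so 124. The t-test gives 124.04. The closest match found is the single-sample formula, (14 × 2.80 / 5)² ≈ 62 in total, about 31 per arm. It is not valid for comparing two arms, and the protocol does not say it was used.

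**2. Power with the stated inputs.** The standard error of the difference is 14 × √(2/30) = 3.61, and 5 / 3.61 = 1.38. The normal approximation gives Φ(1.38 − 1.96) = 28.2%; the noncentral t gives 27.5%.

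| Variant (t-test) | Power |
|---|---|
| 30 per arm, two-sided | 27.5% |
| 33 per arm (no dropout), two-sided | 29.8% |
| 30 per arm, one-sided 0.05 | 39% |
| 8.7 points (11% of 79.4), 30 per arm, two-sided | 66% |
| 8.7 points, 33 per arm, two-sided | 70% |
| 8.7 points, 30 per arm, one-sided | 77% |

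**3. What 30 per arm can do.** The standardised difference detectable with 80% power is 0.736, and 0.736 × 14 = 10.3 points, about twice the stated effect. Put the other way, 5 points would need an SD of 5 / 0.736 = 6.8. The expected 95% confidence interval half-width is 2.00 × 3.61 = 7.2 points.

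**4. Allowing for the planned model.** The correlation r below is an assumption, taken as equal between all visits. With baseline as covariate, the variance is multiplied by 1 − r² for one follow-up. For a group effect averaged over two follow-ups it is multiplied by (1 + r)/2 − r². Power for 5 points, 30 per arm, two-sided:

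| r | One follow-up | Two follow-ups averaged |
|---|---|---|
| 0.5 | 35% | 49% |
| 0.7 | 48% | 62% |
| 0.8 | 62% | 76% |
| r needed for 80% | about 0.87 | about 0.82 |

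**5. The percentage and the direction.** 5 / 79.4 = 6.3%, whereas 0.11 × 79.4 = 8.7 points. For 5 points to be 11%, the base would have to be 5 / 0.11 = 45.5, which appears nowhere in the protocol. As to direction, section 4.3 has a reduction favouring the intervention, while section 1 has an increase in self-reported health status, for which the SIS is the named measure (section 6.1.1). This is a conflict of wording and does not change the power.

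**The case against.** The strongest reply is that 27% is not the power of the planned analysis. Section 8.2 foresees a multilevel model over two follow-ups, possibly with baseline values, and such a model can be considerably more efficient than a single-visit t-test. This stands in part, and it rules out the stronger reading that the trial's actual power is 27%: that figure belongs to an unadjusted comparison. Nor can one say that a correlation of 0.87 is always needed, because averaging two follow-ups lowers it to about 0.82. The reply still does not support 80%. Section 4.3 claims no such gain, no correlation is stated, section 8.2 does not commit to an averaged effect, and baseline values enter only if significant.

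The second reply is that this is a pilot, as sections 2 and 3 call it. A pilot may be small, and the label softens the risk of misreading a null result. It does not justify a power figure that the inputs do not give. Section 2 also names clinical effectiveness among the main aims.

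A reader might infer three further things that the protocol does not support. One is that the power figure will carry over into the announced phase III trial; section 1 says only that this study is its basis. Another is that 6.3% is the correct percentage; the base of the 11% is not given, so 5 points or 11% could be the slip. The third is that the study expects harm on the SIS; the phrase about favouring the experimental group shows that benefit was meant.

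**Conclusion.** The claim of "a sufficient statistical power of 80" per cent is wrong on the inputs printed beside it. For 5 points, SD 14 and 30 per arm, power is about 27% if the test is two-sided and unadjusted, and 39% if one-sided. About 124 per arm would be needed for 80%, roughly four times the plan. Reading the effect as 8.7 points raises two-sided power only to about 66%. Combining that reading with a one-sided test gives 77%, but this contradicts the stated 5 points and adds an unstated assumption.

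The exact percentage depends on sidedness and on the analysis model, neither of which section 4.3 fixes. Under adjustment at assumed correlations of 0.5 to 0.8, power lies between about 35% and 76%. The conclusion that 80% is unsupported holds across that range. The mismatch between 5 points and 11%, and the word reduction, are secondary inconsistencies to reconcile.

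**What to change.** Keep 66 patients and restate section 4.3, for example: *Assuming a two-sided, unadjusted comparison at alpha 0.05 with SD 14, 60 evaluable patients give 80% power for a difference of about 10.3 points on SIS mobility and about 27% for 5 points. The expected 95% confidence interval half-width is about 7.2 points. This pilot estimates the effect and its variance.*

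If a gain from baseline adjustment or repeated measures is to be claimed, state the assumed correlation, its source, and whether the effect is averaged over both follow-ups. Say whether 5 points or 11% was the planned effect, and give the base of the percentage. Reconcile the word reduction with the increase hypothesised in section 1.

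The cost is a wording change in one section and a less favourable power statement, with no extra patients, visits or procedures.

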## 5. TREATMENT OF SUBJECTS

### 5.1 Investigational treatment

The CARE4STROKE program consists of eight weeks of complementary exercise therapy done with a caregiver, next to the usual therapy. 31 standardized exercises are available, that can be customized per patient and caregiver into an individualized program. These exercises were devised in collaboration with movement scientists and physical therapists and were shown to be feasible in the pilot study in Reade. The exercises are presented in an E-health application (app) for a tablet. Regular reminders to exercise can be given by the app. The exercises are aimed at improving skills related to walking ability like sitting, standing and making transfers, or are supporting exercises to improve mobility, strength and balance. The patient and their caregiver are asked to do the exercises minimally 5 times a week for 30 minutes on at least both weekend days or the equivalent dosage with an adopted schedule. When the intervention is correctly performed patients will have a surplus of 150 minutes of caregiver mediated therapy a week.

Patients and their caregiver will have a weekly session with a trained therapist. In this session, the participating couple will be instructed as to which exercises should be performed safely during the next week and evaluate the exercises done last week. All patients and caregivers will be supported by a handbook with instructions.

The program starts when the patient is admitted in one of the participating centres. When the discharge date of the patient is earlier than the finishing of the program, the program continues at home with continuous monitoring from the treating therapist.

### 5.2 Control treatment

The participants in the control group will receive usual care according to the Dutch guidelines for patients with stroke and the Royal Dutch Guidelines of Physical Therapy.

### 5.3 Use of co intervention

All patients that receive usual care will not be enrolled in other studies. During the study, usual care will be recorded. Participants in both the intervention and control group will use a diary to register every therapy and (self) training session.

## 6. METHODS

### 6.1 Study parameters/endpoints

#### 6.1.1 Main study parameters

For the patient:

- 1) Length of Stay in the HSU, RC or NH, defined as the moment of admittance-moment of discharge. (primary outcome)
- 2) Self reported health status with the Stroke Impact Scale (SIS version 3.0) 
- 3) Quality of life, measured with the EQ-5D. 
- 4) Mobility, measured by the Rivermead mobility index (RMI) 
- 5) Independence in performing basic activities of daily living, measured by the Barthel index (BI) 
- 6) Walking ability, assessed with the 5 metre walking speed, the 6 minute walking test and the timed up and go test (TUG). 
- 7) Extended Activities of daily living, measured by the Nottingham extended ADL (NEADL). 
- 8) Functional outcome, measured by Modified Rankin Scale (MRS) dichotomised to good outcome (0-2) or poor outcome (3-6). 
- 9) Balance, assessed with the Berg Balance Scale (BBS) 
- 10) Selectivity lower extremity, assessed with the Fugl Meyer (FM) lower extremity. 
- 11) Strength of the lower limb, assessed with the Motricity Index (MI). 
- 12) The amount of daily activity, assessed with a comfortable and wireless activity monitor on the wrist.

For the caregiver:

- 13) the experienced strain of the caregiver measured by the Expanded Caregiver strain index. (CSI +) 
- 14) Quality of life, measured with the CareQOL. 

For both:

- 15) Amount of (additional) practice done by the couples in the intervention and controlgroup, this will be measured with a diary (see appendix) Problems and adverse events like falls will also be recorded in the diary
- 16) Personal Opinion Questionnaire for empowerment .

- 17) Emotional functioning, measured with the Hospital Anxiety and Depression Scale (HADS).
- 18) Fatigue, measured by the fatigue severity scale.
- 19) Self-efficacy, measured by the general self-efficacy scale.
- 20) A cost diary, comprising questions on items such as consultation with neurologists, family doctors, paramedics, re-admission to hospitals or rehabilitation centres, drug use, home care and non-professional support.

Outcome measures will be measured at baseline prior randomization, after the eight week intervention period and again after 12 weeks (follow up) by a blinded assessor who is not involved in training. Length of stay in the rehabilitation center will be reported at discharge of the patient. Self reports in the (cost)diary will take place during the intervention. To assess the long term costs, some patients will be asked to keep the cost diary until the end of the study in 2016. These data will be obtained by the blinded assessor with telephone interviews.

In addition, at the end of the intervention, semi-structured interviews will be conducted with some patients and caregivers to collect qualitative data regarding the experience of CME.

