### Main study parameters/endpoints:

Primary measurements of outcome: 1) Length of Stay and 2) self-reported health-status with the Stroke Impact Scale (SIS version 3.0). Secondary outcomes for included stroke patients are EuroQol-5D (EQ-5D), the Barthel Index, Rivermead Mobility Index, Berg Balance Scale, 5 meter walking speed, 6 minute walking test, Timed Up and Go Test, the Motricity Index (leg), The Fugl-Meyer assessment (leg), Nottingham Extended Activities of Daily Living and modified Rankin Scale. In order to track the daily activity, patients will wear a wireless activity monitor on the wrist one week before and after the intervention. In addition, patients keep a

diary to record adherence to the exercise program and emerging complications. Caregiver burden will be evaluated with the Caregiver Strain Index and Carer Quality of Life Index. For patients and caregivers the Hospital Anxiety and Depression Scale, Fatigue Severity Scale, General self-efficacy scale and Personal Opinion Questionnaire for empowerment will be used. In addition each couple will use a cost diary.

**Nature and extent of the burden and risks associated with participation, benefit and group relatedness:** Participants in the intervention group get a surplus of 150 minutes of exercise training a week; Caregivers will be involved and will need to allocate time to the programme as well. Care is taken to assure safe performance of the exercises. This will be accomplished by e-health and tele-rehabilitation services and safety instructions and close guidance and coaching of a therapist. The control group will have no additional benefit or risks. Assessments will take place at baseline, after the intervention and at twelve weeks follow up. They consist of questionnaires and tests, taking approximately two hours per assessment.

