### **6.3 Study procedures**

Every patient with stroke, admitted in one of the participating centres, will be screened for eligibility by their own treating medical specialist to evaluate if participation in this study is possible. On a registration form will be noted: if a person is asked, if this person wants to participate, and what the considerations were. An information letter is handed to patient and caregiver and a reflection period of one week will follow. Eligible patients and their chosen caregiver will be informed in an interview with the primary researcher and a therapist will judge if the caregiver can adequately assist the patient during exercises. Upon inclusion, informed consent will be signed. Thereafter the baseline measurements will be done (T0).

The couples will be randomly allocated to either the intervention or control group.

For the couples allocated to the intervention group the intervention starts directly. After eight weeks the same measurements as at baseline will be repeated (T1) for every couple. Follow up measurements will be performed 12 weeks post randomisation.

(see figure 1)

The assessments consist of clinical tests and questionnaires (see outcome measures). The assessments and inclusion will be done by an assessor who is blinded to treatment allocation.

Prior to starting the inclusion of patients, all therapists will be extensively trained in applying the CARE4STROKE programme to optimize standardization with regard to coaching the participants and performing the weekly training sessions in which patient and partner learn the exercises.

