### 8.3 Cost-effectiveness analysis

A cost effectiveness and a cost-utility analysis will be performed The primary outcome of the trial, length of Stay, in combination with the information of the cost diary will be used in the cost effectiveness analysis. Unit costs will be taken from national sources.

In the costs utility-analysis the outcome measure is quality-adjusted life-years (QALYs) based on the Dutch tariff for the Euro(QoI).

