### 9.2 Recruitment and consent

In the first week of admittance in one of the participating centres, every patient with stroke will be screened by their own treating medical specialist to evaluate if participation in this study is possible. Eligible patients and their chosen caregiver will be informed in an interview with the primary researcher and a therapist will judge if the caregiver can adequately assist the patient during exercises. A reflection period will follow. Upon inclusion, a second interview with the primary researcher will follow and informed consent will be signed. Next the baseline measurements will be done. Randomisation will follow and treatment starts as soon as possible after that.

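### The primary outcome counts length of stay from admission, but the enrolment sequence puts randomisation about 7 to 14 days later: this adds noise rather than bias, and a short stay can end before allocation

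*Protocol*

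**What the plan says.** **Outcome.** Section 6.1.1 lists LOS first and labels it primary, "defined as the moment of admittance-moment of discharge". Section 8.3 uses it again in the economic analysis: "The primary outcome of the trial, length of Stay, in combination with the information of the cost diary". The hypotheses at the end of section 1 give the expected gain as 1 day in the HSU and 7 days in the rehabilitation centre (RC) or nursing home (NH).

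**Start of the programme, first account.** Section 3: "Patients will start immediately after admission". Section 5.1: "The program starts when the patient is admitted in one of the participating centres". Section 2 says the same of both the exercises and the app.

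**Start of the programme, second account.** Section 9.2: "In the first week of admittance in one of the participating centres, every patient with stroke will be screened". Section 6.3: "An information letter is handed to patient and caregiver and a reflection period of one week will follow". Consent and baseline measurement (T0) come next. Section 6.1.1 confirms that baseline precedes randomisation, and section 9.2 places treatment after randomisation.

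**Eligibility.** Sections 4.1 and 4.2 require admission to a participating centre, a planned discharge home and an intake exercise session. They set no minimum remaining stay and no rule for a patient who goes home before allocation.

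**The concern.** The two accounts of when the programme starts cannot both hold if the reflection week and the pre-randomisation baseline are observed. If the enrolment sequence is followed, the primary outcome contains one to two weeks that end before the arms differ.

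Two things follow. First, variation between patients in that interval can enter the LOS comparison as noise, and this matters most where the expected effect is smallest, in the HSU. Second, a stay that ends during the reflection week is fixed before allocation. If such a patient is then randomised, the LOS effect for that patient is zero by construction and the average effect is diluted.

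**Working it through.** The protocol gives no mean, SD or sample size for LOS (section 4.3 is based on the SIS mobility domain), so it has no LOS figure to reproduce.

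**Step 1: interval from admission to randomisation.**
- Screening: day 0 to day 7 (section 9.2, first week).
- Reflection: 7 days (section 6.3; section 9.2 mentions a reflection period without a length).
- Consent, T0 and allocation: no duration given beyond about two hours per assessment (Summary).

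Earliest: 0 + 7 = 7 days. Latest: 7 + 7 = about 14 days, plus any time for the last group of steps. This is 7 to 14 times the 1-day HSU effect and 1 to 2 times the 7-day RC/NH effect.

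**Step 2: bias.** Write T = L + R, where T is the stay from admission, L the interval to randomisation and R the remaining stay. L is settled before allocation, so its expectation is equal in both arms and the expected difference in T equals that in R.

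**Step 3: noise.** Assume the screening day is uniform over 0 to 7, so SD(L) = 7/√12 = 2.02 and Var(L) = 4.08. Assume also that R is independent of L. Then Var(T) = Var(R) + 4.08. The standard error (SE) for one centre of 22 patients, split equally (assumed), is SD × √(2/11).

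| Assumed SD of R (days) | Rise in variance | SE from randomisation | SE from admission |
|---|---|---|---|
| 3 | 4.08/9 = 45% | 1.28 | 1.54 |
| 5 | 4.08/25 = 16% | 2.13 | 2.30 |
| 10 | 4.08/100 = 4% | 4.26 | 4.35 |
| 20 | 4.08/400 = 1% | 8.53 | 8.57 |

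**Step 4: dependence on the independence assumption.** If instead T is unrelated to L (discharge follows recovery since admission), then Var(R) = Var(T) + Var(L), and counting from randomisation is the noisier choice. A covariate removes the difference. If R = a + b·group + c·L + e, then T = a + b·group + (c + 1)·L + e. The group coefficient b and the residual e are identical, so with L in a linear model the origin no longer affects the estimate.

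**Step 5: stays that end before allocation.** With screening on day 0, any stay under 7 days is over before randomisation; with screening on day 7, so is any stay under about 14 days. If a share p of randomised patients has already gone home, an effect of d days among the others averages (1 − p)·d. The protocol gives no HSU stay from which to obtain p. As an illustration only, for an assumed lognormal stay with log-SD 0.6, the shares of stays shorter than 7 and 14 days are 50% and 88% at a median of 7 days, 18% and 60% at 12 days, and 3% and 25% at 21 days. The spread shows that the documents cannot settle the frequency.

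**The case against.** The case for leaving the definition alone is substantial. Total stay is what the hypothesis and the cost analysis are about, the comparison is unbiased, and a reduction of 1 or 7 days is the same number from either origin. For long RC/NH stays the added noise is negligible. Section 8.2 plans one model with location in it, so an HSU-only comparison is not the stated analysis. Section 4.1 has patients approached at admission, which points to the lower end of the range, and its wording about admitted patients planned to go home suggests that discharged patients were not meant to be enrolled. All of this stands, but no criterion says so, and the start-time contradiction remains.

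A reader might also infer stronger points that the documents do not support:

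- **A three-week interval.** The Summary says "patients will wear a wireless activity monitor on the wrist one week before and after the intervention". That week precedes the intervention, not necessarily randomisation, and may overlap the reflection week.
- **An extra HSU standard error of 0.86 day, hence limits of ±1.7 days.** The figure 2.02 × √(2/11) = 0.86 is one component. It combines in quadrature: √(1.28² + 0.86²) = 1.54, an increase of 0.26 day at SD 3 and only 0.04 at SD 20.
- **A 1-day HSU reduction that cannot be achieved.** Without an HSU length of stay this cannot be judged.
- **A sure gain in precision from moving the origin.** Step 4 shows that this depends on how remaining stay relates to the interval.

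**Conclusion.** The point holds as a weakness in how the primary outcome is fixed, together with a contradiction between sections 2, 3 and 5.1 and sections 6.1.1, 6.3 and 9.2. If the enrolment sequence is followed, about 7 to 14 days of LOS lie beyond the reach of allocation. They cause no bias. Their cost in precision runs from about 45% extra variance at a post-randomisation SD of 3 days to 1% at SD 20, given an interval SD of 2.0 days and independence, neither of which the protocol states. The gap about patients discharged before allocation needs no variance assumption: it is possible under the text, its effect is dilution towards zero, and its frequency is unknown. The point is worth correcting because the correction is cheap, but it does not invalidate the comparison.

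**What to change.** - **Section 6.1.1 and eligibility:** limit the LOS comparison to patients still admitted at randomisation. This status is known before allocation, so the restriction introduces no bias.
- **Section 8.2:** analyse LOS from randomisation to discharge with the admission-to-randomisation interval as a covariate. Report admission-to-discharge LOS as well, which also serves the economic analysis.
- **Sections 2, 3 and 5.1 against 6.1.1, 6.3 and 9.2:** reconcile when the programme starts relative to admission, consent and randomisation.

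The cost is a few sentences and one more covariate. It needs three dates: LOS already requires admission and discharge, and the 12-week visit, timed from randomisation, requires the third. The new figure is less directly comparable with published total LOS, which is why both should be reported.
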